# Efficacy and safety of *Qing-Feng-Gan-Ke Granules* in patients with postinfectious cough: study protocol of a novel-design phase III placebo-controlled, double-blind randomized trial

**DOI:** 10.1186/s12906-015-0812-3

**Published:** 2015-08-19

## Abstract

**Background:**

Postinfectious cough (PIC) is a common condition that affects millions of people worldwide every year. There is Western medicine for this condition but the treatment effect is often incomplete. Traditional Chinese medicine (TCM) has been increasingly prescribed for patients with PIC. Preliminary trials on *Qing-Feng-Gan-Ke-Granules* (QFGKG) conveyed promising results in treating PIC. This protocol describes an ongoing phase III randomized controlled clinical trial, designed according to a novel methodology of “one study, one primary outcome”, with the objective of evaluating the efficacy and safety of QFGKG in patients suffering from PIC.

**Methods/Design:**

This is a multicenter, phase III, randomized, double-blind, parallel-group, placebo-controlled clinical trial, comprising two simultaneously conducted study parts, part A and part B, intending to investigate two primary outcomes, *i.e.* time to cough resolution and cough symptom score, respectively. A total of 480 patients, aged 18 to 65 years, who complain of an ongoing persistent cough that has been lasting ≥3 weeks, will be recruited from six participating sites and then randomized to receive QFGKG 12.0 g twice daily or placebo 12.0 g twice daily. Each part will enroll 240 patients, with 180 patients being allocated to the QFGKG group and 60 to the placebo group.

**Discussion:**

Although traditional Chinese medicine is a structured intervention that has shown some promise in treating persistent cough, existing unconvincing evidence has noted limitations. This is a rare well-designed and rigorously-controlled, randomized, double-blind trial to evaluate the effects and safety of a Chinese herbal medicine in patients with postinfectious cough, providing tangible benefits for clinical research. Results of this trial are inclined to be conjectured as more truthful by implementing separate study parts that specifically estimate exclusive primary outcome. It will not only provide robust clinical evidence on the efficacy and safety of QFGKG for postinfectious cough, but will also provide a critical piece of information on the availability and superiority of a novel methodology for future clinical trials. The current trial is ongoing with recruitment of the predetermined number of patients being in progress.

**Trial registration:**

The two parts of this trial were separately registered with the Chinese Clinical Trial Registry: ChiCTR-TRC-13003278 (part A); and ChiCTR-TRC-13003337 (part B).

## Background

Cough is the most common symptom presenting to primary healthcare services. Postinfectious cough (PIC) is considered as one of the top causes of subacute cough, which occurs in 11 to 25 % of patients with upper respiratory tract infection (URTI) [1, 2]. It involves a persistent cough lasting ≥3 weeks or even months [3] (but normally < 8 weeks) secondary to the acute symptoms of a common cold or upper respiratory tract infection (URTI) [4, 5]. Although PIC is always self-limited and is not associated with severe debilitation or mortality, persistent cough may impair the quality of daily life [4]. Therefore, many patients with PIC are frequently impelled to seek medical help [6].

Aside from pertussis, however, despite the fact that many pathogenic agents including respiratory viruses (particularly respiratory syncytial virus, adenoviruses, parainfluenza, and influenza), M pneumoniae and Chlamydophila pneumoniae have been implicated in children [4, 5, 7], the role of infectious aetiology in PIC in adults is rarely confirmed till now [8]. Poor knowledge on the pathogenesis of PIC, which is supposed to be frequently multifactorial [2, 8–10], results in a diagnostic challenge for physicians. Patients are constantly investigated for other causes of persistent cough [6]. Therapy with antibiotics has no role, as there is no evidence that bacterial infection plays a role in adult patients [4, 5]. Cysteinyl leukotrienes were considered to be involved in the pathogenesis of PIC in recent studies, however, montelukast failed to effectively treat PIC in a latest randomized trial [11], leading to a controversy on its role in PIC. Therefore, PIC can be a troublesome problem for physicians and patients alike [6]. Currently available therapies, including inhaled ipratropium, inhaled or oral corticosteroids, central acting antitussive agents such as codeine and dextromethorphan, can only be used for symptom relief [4–7, 12, 13]. They have not been proved to be effective in reducing the cough duration or improving the quality of life [4]. And above all, a range of adverse outcomes including blurred vision, confusion, difficulty in urination, drowsiness or dizziness, body rash/itching, nausea or vomiting, constipation, diarrhea, sedation, nervousness are elicited occasionally [14–16]. For these reasons, complementary and alternative medicine is becoming more and more popular in patients with PIC, such as a combination of honey and coffee [6] as well as traditional herbal medicines.

The use of traditional Chinese medicine (TCM) as a complementary and alternative therapy for cough can be dated back to thousands of years ago. People in China who suffer from a persistent cough always give first priority to TCM. With an increasing number of TCM formulas developed for clinical use, an overview to facilitate the discussion of its pros and cons is warranted. A recent comprehensive systematic review of randomized controlled trials demonstrated potential curative effects and reassured the safety of TCM in the management of PIC [17]. Unfortunately, due to the undesirable quality of included studies, the definite effect of TCM turned to be inconclusive in this review. Therefore, a rigorously designed randomized trial becomes imperative.

TCM offers a holistic vision on disease, and syndrome differentiation is the cornerstone of TCM prescription. Differentiation means comprehensive analysis, and syndrome refers to symptoms and signs. Differentiation of syndromes implies that the patient’s symptoms and signs collected by the four diagnostic methods (inspection, auscultation ant olfaction, inquiry, pulse-taking and palpation) are analyzed and summarized to identify the etiology, nature and location of a disease, thereby determining what syndrome the disease belongs to. Based on both clinical experience and literature review, “pathogenic-wind invading lung syndrome” is considered as the most common TCM syndrome in patients with PIC [17]. TCM patent drug *Qing-Feng-Gan-Ke-Granules* (QFGKG), designed on the basis of a classic formula, comprises four widely used herbal plants (*Ephedra sinica Stapf*, *Sinomenium acutum*, *Stemona japonica (Blume) Miq.*, and *Aster tataricus L.f.*). It has been shown that QFGKG is very effective in dispelling wind and relieving cough and is specifically appropriate for treating “pathogenic-wind invading lung syndrome”. Unpublished preliminary phpartacodynamics studies in rats showed that QFGKG could significantly alleviate sulfur dioxide-induced cough and ammonium hydroxide-induced cough, increase the tracheal phenolsulfonphthalein excretion, improve the peritoneal capillary permeability reduced by acetic acid, relieve asthma caused by acetyl choline and histamine inhalation, inhibit carrageenin-induced toes swelling, suppress dinitrochlorobenzene-induced delayed type hypersensitivity, which suggests its antitussive, anti-inflammatory and immunosuppressive properties. Subsequent clinical studies investigated its efficacy and feasibility in individuals with PIC [18, 19]. In addition, a previous multi-center phase II trial [20] investigated the dose-effect relationship and dose-safety relationship of QFGKG, with primary outcomes of time to cough relief and time to cough resolution, as well as secondary outcomes of cough symptom score, cough recovery rate, TCM curative effect, and Chinese version of cough-specific quality of life questionnaire (CQLQ) score [21]. In this phase II trial, 180 patients were enrolled and randomly assigned to receive high dose of QFGKG (12.0 g, twice daily), or low dose of QFGKG (6.0 g, twice daily) plus dummy QFGKG (6.0 g, twice daily), or dummy QFGKG (12.0 g, twice daily) alone. Great improvements in all outcomes, especially the time to cough resolution and cough symptom score, were observed in the high dose group. To the best of our knowledge, the phase II study was the first well-designed placebo-controlled clinical trial that reported TCM as a remedy for PIC, and its resultful conclusions provide foundations for the current phase III trial.

“One study, one primary outcome”, a novel methodology for clinical trial design, was published by China Food and Drug Administration (CFDA). The core of this concept lies in the supposition that study results will be more credible if the whole study is single-mindedly and exclusively designed for the unique outcome of main interest. Moreover, the SPIRIT guidance suggests a minimum number of primary outcomes in clinical trials because multiple primary outcomes can introduce problems with multiplicity, selective reporting, and interpretation when there are inconsistent results across outcomes [22]. Thus, although this design has not been widely implemented in clinical trials, we prefer to conduct a tentative trial in an attempt to provide some practical information.

The objective of this trial is to demonstrate the superior efficacy and safe of QFGKG over placebo in adult individuals with PIC by addressing the following hypotheses: (1) That QFGKG will significantly shorten the cough duration in patients with PIC; (2) That QFGKG will significantly relieve the main clinical symptoms in patients with PIC; (3) That QFGKG will increase the quality of life in patients with PIC; (4) That QFGKG is safe and will not result in any serious side effects; (5) That the novel design methodology of “one study, one primary outcome” is feasible and desirable in clinical trials.

## Methods/Design

### Study designs

This trial is designed as a randomized, double-blind, placebo-controlled, parallel, phase III, superiority trial, with allocations stratified by participating centers and randomization performed as block at a ratio of 3:1, adhering to the recommendation of “CONSORT statement” [23] and “SPIRIT statement” [24]. As to the allocation ratio, generally speaking, for a superiority trial using placebo as a control intervention, 3:1 is recommended by Provisions for Drug Registration (http://www.sda.gov.cn/ypzcgl/ml.htm), taking into full consideration of statistical significance, ethical requirement and risk-cost relationship. This trial consists of two simultaneously conducted study parts (part A and part B), currently involving six participating centers across China: West China Hospital of Sichuan University, Tangdu hospital of The Fourth Military Medical University, Affiliated Hospital of Jiangxi University of TCM, the Second Affiliated Hospital of Tianjin University of TCM, Affiliated Hospital of Inner Mongolia Medical University, and the First Affiliated Hospital of Henan University of TCM. These centers were defined primarily geographically. In each participating center, a chief investigator will be appointed to be responsible for the whole clinical process (subject recruitment, intervention, follow-up, and data collection), adhering to the study protocol. All personnel involved in this trial will be trained prior to trial initiation. Training program is about study protocol and relevant skills, especially the skill of TCM syndrome differentiation. Staff placement and individual responsibility will also be elaborated in the training session. Besides, investigator’s brochure developed by the sponsor to facilitate the smooth running of the trial will also be provided. This protocol is designed largely depending on the results of previous phase II trial. Both study parts have been registered with Chinese Clinical Trial Registry (http://www.chictr.org). This protocol has two amendments. The schematic diagram and flow chart of study process are shown in Tables 1, 2 and Fig. 1.

**Table 1 Tab1:** Schematic diagram of part A

Phase	Supervision period			
Time-point	Baseline	Visit 1	Visit 2	Visit 3
Day	0	8 ± 1	15 ± 2	Follow-up
Basic history collection	×			
Informed consent	×			
Demographics	×			
Enrollment based on the inclusion/exclusion criteria	×			
Coexisting diseases or symptoms	×			
Concomitant treatments		×	×	
Efficacy evaluation				
Cough symptom score	×	×	×	×
TCM syndrome score	×	×	×	
Safety evaluation				
Vital signs	×	×	×	
Blood routine and urine routine	×		×	
Liver function (ALT, AST, STB, ALP, γ-GT )	×		×	
Renal function (Cr, BUN)	×		×	
ECG	×		×	
Adverse events		×	×	
Screening tests				
CR	×			
BPT	×			
UPT (women of childbearing age)	×			
Other steps				
Randomization allocation	×			
Drug distribution	×			
Remaining drug count			×	
Patient record card distribution/recycling	×		×

**Table 2 Tab2:** Schematic diagram of part B

Phase	Supervision period			
Time-point	Baseline	Visit 1	Visit 2	Visit 3
Day	0	6 ± 1	11 ± 1	Follow-up
Basic history collection	×			
Informed consent	×			
Demographics	×			
Enrollment based on the inclusion/exclusion criteria	×			
Coexisting diseases or symptoms	×			
Concomitant treatments		×	×	
Efficacy evaluation				
Cough symptom score	×	×	×	×
Cough VAS score	×	×	×	
TCM syndrome score	×	×	×	
CQLQ	×		×	
Safety evaluation				
Vital signs	×	×	×	
Blood routine and urine routine	×		×	
Liver function (ALT, AST, STB, ALP, γ-GT )	×		×	
Renal function (Cr, BUN)	×		×	
ECG	×		×	
Adverse events		×	×	
Screening tests				
CR	×			
BPT	×			
UPT (women of childbearing age)	×			
Other steps				
Randomization allocation	×			
Drug distribution	×			
Remaining drug count			×	
Patient record card distribution/recycling	×		×

**Fig. 1 Fig1:**
[figure not shown]
Flow chart of study process

### Study participants

A total of 480 patients will be recruited and averagely assigned to each part. Each center will recruit an equal number of patients; 60 patients will be recruited at each individual center in part A and 80 patients will be enrolled at each individual center in part B. Patients, who are diagnosed as having PIC in one of the participating centers according to the guideline issued by the Chinese Medical Association [25], aged between 18 and 65 years, with a TCM syndrome being differentiated as “pathogenic-wind invading lung” based on the Guidelines for Clinical Research of New Chinese Medicine [26], are eligible for enrollment. Diagnosis criteria of PIC are presented in Table 3. Inclusion and exclusion criteria are listed in Table 4, and TCM syndrome diagnostic criteria, based on State Administration of Traditional Chinese Medicine guidelines [27], are elaborated in Table 5. Some discrepancies should be noticed in the inclusion criteria of two parts. Part A is designed to focus on the time when cough can be resolved completely, thus patients’ cough severity is relatively mild in order to yield more expected results. On the other hand, part B is designed to calculate the dynamic change in cough symptom score across four time-points (see Table 2), so the cough severity of patients recruited in this part is relatively severe for more obvious changes.

**Table 3 Tab3:** Diagnosis criteria for postinfectious cough

● Cough that has been present following symptoms of an upper respiratory tract infection;
● Irritable dry cough or cough with small amounts of white mucus;
● Cough lasts for at least 3 weeks, but normally no longer than 8 weeks;
● Negative findings of chest radiograph;
● Negative results of bronchial provocation test and dilation test;
● Exclude other causes which could result in cough, such as upper airway cough syndrome(UACS), cough variant asthma(CVA), eosinophilic bronchitis(EB) and gastroesohageal reflux disease(GERC);
● Exclude severe pulmonary diseases including chronic obstructive pulmonary disease(COPD),lung cancer, pulmonary tuberculosis, et al.;
● Exclude hypertension that involves use of angiotensin converting enzyme inhibitor(ACEI) currently.

**Table 4 Tab4:** Selection criteria for eligible patients

● Inclusion criteria for study part A	● Inclusion criteria for study part B
● Postinfectious cough	● Postinfectious cough
● Syndrome of “pathogenic-wind invading lung”	● Syndrome of “pathogenic-wind invading lung”
● Daytime cough symptom score ≥ 2 and/or nighttime cough symptom score ≥ 2	● Total cough symptom score ≥ 4
● Persistent cough ≥ 3 weeks and ≤ 6 weeks	● Persistent cough ≥ 3 weeks and ≤ 6 weeks
● Age 18-65 years old	● Age 18-65 years old
● Agreement to participate and provision of informed consent	● Agreement to participate and provision of informed consent
● Exclusion criteria	
● Body temperature > 37.3 °C	
● Use of any medication intended to treat PIC within one week before enrollment	
● ALT/AST > 1.5 times than the upper limit of normal reference values; Abnormal blood creatinine; Urine protein qualitative test > +; Blood leukocyte count < 3.0 × 10^9^/L or > 10.0 × 10^9^/L; and/or neutrophil percentage > 80%	
● History of any severe underlying diseases (*e.g.* cardiovascular, hematological, hepatic, renal); or other life-threatening disabling conditions and concomitant diseases (*e.g.* cancer, AIDS)	
● Pregnancy or potential pregnancy or lactation	
● Hypersensitivity or allergy to any component of the test drug	
● Current psychiatric disorders or legal disability	
● Current or previous admission to other investigational drug studies within 3 months before enrollment	
● Inability to complete the trial as decided by the investigators

**Table 5 Tab5:** Diagnostic criteria for TCM differentiation of “pathogenic-wind invading lung syndrome”

Item	Symptoms and signs
*Primary symptom	persistent cough
Secondary symptoms	1) *throat itching, cough sensitivity to cold air, heat air or strange odors and/or;
	2) sticky and scanty sputum, dry throat and chest congestion
*Tongue picture	slight red tongue proper with/without red tip; thin white tongue coating
*Pulse condition	normal or floating pulse

* Items which must be satisfied for a diagnosis of TCM differentiation of “pathogenic-wind invading lung syndrome”

Patients must provide written informed consent before any study procedures occur. Participants would be excluded if they have any of the following conditions: 1) misdiagnosis; 2) poor drug compliance (taking < 80 % or > 120 % of the required dosage); 3) inability to complete the follow-up; 4) aggravations (such as dyspnea) that happen within 24 h after taking the test drug (on this occasion, patients will be treated with conventional therapies and considered as an invalid case, whose last data would be collected in Full Analysis Set (FAS)); 5) hypersensitivity or other severe adverse reactions; and 6) voluntary withdrawal. The trial will be terminated prior to its planned end date in the context of the following accidents: 1) protocol deviations; 2) inadvisable or flawed protocol; 3) compelling suspension forced by authoritative agencies; and 4) discontinuation decided by the trial sponsor (managerial or financial difficulties).

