#### Part B

##### Primary outcome

The primary outcome of part B is cough symptom score, which will be assessed across baseline, 6 ± 1 days into the intervention, post-intervention (11 ± 1 days) and 2 days post-intervention if necessary. Simplified cough symptom score (SCSS) recommended by Chinese Medical Association [30] is developed based on the Asthma and Cough Symptom Score Estimation Method [31]. It consists of daytime score and nighttime score, ranging from 0 to 3, respectively. The cough symptom score scale is provided in Table 7. SCSS, which is usually used to determine the frequency and diurnal variation of cough, and also to reflect the quality of life, has been verified as reproducible and well-responsive to treatments [32]. Daytime is arbitrarily defined as 8 a.m. to 8 p.m. and nighttime as 8 p.m. to 8 a.m.

**Table 7 Tab7:** Cough symptom score scale

Score	Daytime cough symptom score	Nighttime cough symptom score
0	no cough during the day	no cough during the night
1	occasional cough for short periods	cough for short periods before sleep or occasional cough during the night
2	frequent coughing, which did slightly interfere with usual daytime activities	frequent coughing, which did slightly interfere with sleep
3	distressing coughs, which did seriously interfere with usual daytime activities	distressing coughs preventing any sleep

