In this trial, we conduct two simultaneous study parts that are mutually independent but not mutually exclusive. We aim to not only propose a new effective remedy for PIC but also practice a novel methodology for clinical trials, that is “one study, one primary outcome”. As we all know, a well designed clinical trial is always expected to answer multiple main clinical questions. Nevertheless, sometimes it is unreasonable to assess multi-primary outcomes in one study. In this trial, we intend to investigate the effectiveness of QFGKG on different clinical outcomes. In this case, it may be more convincing and persuasive to study different groups of patients and conduct different intervention durations to achieve exclusive primary outcome by separating the original trial into study parts. We believe that if considering the results of the two study parts as a whole, it would be helpful not only for figuring out ongoing objectives but also for clarifying further implications. Therefore, we assume that this novel design contributes to maximized efficacy, lower cost, a better risk-benefit ratio of treatment and more convincing results with strong application value and may be recommended for further clinical intervention trials. This is the most all-important distinguishing feature of this trial. Another breakthrough in this protocol is that we highlight the importance of two clinical related outcomes, time to cough resolution and quality of life, which are seldom assessed in previous studies [14].

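### Part A is described as a mild-cough population, but its entry criterion is only a floor that admits every part B score pattern, so its primary outcome mixes baseline severities the protocol treats as prognostic

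*Protocol article*

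**What the plan says.** Study participants explains why the inclusion criteria of the two parts differ. Part A studies the time to complete resolution, so its patients' "cough severity is relatively mild in order to yield more expected results". Part B follows the change in score, "so the cough severity of patients recruited in this part is relatively severe for more obvious changes".

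Table 4 then gives the criteria:

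- Part A: "Daytime cough symptom score ≥ 2 and/or nighttime cough symptom score ≥ 2".
- Part B: "Total cough symptom score ≥ 4".

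The other inclusion criteria are the same in both columns, including cough duration ("Persistent cough ≥ 3 weeks and ≤ 6 weeks"), and one exclusion list serves both parts. The score is defined under Part B, Primary outcome: "It consists of daytime score and nighttime score, ranging from 0 to 3, respectively".

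The Discussion gives as a reason for separate parts that they "study different groups of patients and conduct different intervention durations". It also says that the parts do not exclude one another. Its limitations paragraph contrasts milder patients treated for 14 days with more severe patients treated for 10. Table 8 lists Kaplan-Meier and the log-rank test for time to cough resolution. Table 1 shows that the cough symptom score is recorded at baseline in part A.

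**The concern.** A population described as mild would normally be defined by a ceiling. Part A's criterion is a floor: it removes the mildest patients and keeps the most severe. A patient with the maximum score of 3 by day and 3 by night qualifies for part A.

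Two things are at stake. The first is interpretation. The article presents the parts as milder and more severe groups and wants their results considered together, but the criteria do not secure that contrast. The second is the primary analysis of part A. By choosing mild patients to favour complete resolution, the protocol treats baseline severity as prognostic for that outcome. If the enrolled patients span the whole range, resolution times are pooled over a known source of spread. On the protocol's own premise, the more severe patients would also resolve less often and be censored more often.

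**Working it through.** **Inputs.** Daytime and nighttime scores each run from 0 to 3 (Part B, Primary outcome). The entry rules are those of Table 4.

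**Step 1: all patterns.** 4 × 4 = 16 daytime/nighttime pairs, with totals from 0 to 6.

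**Step 2: part A rule (day ≥ 2 or night ≥ 2).** The pairs that fail have both scores at 0 or 1: 2 × 2 = 4 pairs (0/0, 0/1, 1/0, 1/1). So 16 − 4 = 12 pairs qualify, with totals from 2 to 6.

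**Step 3: part B rule (day + night ≥ 4).** Six pairs qualify: 1/3, 3/1, 2/2, 2/3, 3/2 and 3/3, with totals from 4 to 6.

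**Step 4: overlap.** If both scores were 1 or less, the total could not exceed 2. A total of at least 4 therefore forces one score to be at least 2, and all 6 part B pairs satisfy the part A rule.

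| Pairs | Number | Totals |
|---|---|---|
| Eligible for part A only (0/2, 2/0, 0/3, 3/0, 1/2, 2/1) | 6 | 2–3 |
| Eligible for both parts | 6 | 4–6 |
| Eligible for part B only | 0 | – |
| Eligible for neither part | 4 | 0–2 |

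The populations are nested, and 6 of part A's 12 patterns lie in part B's range.

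**Step 5: the stricter reading of and/or.** If both scores had to be at least 2, four pairs would qualify (2/2, 2/3, 3/2, 3/3), all with totals of at least 4. Every part A pattern would then be a part B pattern, so this reading does not restore a mild population.

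**Step 6: could part A still be milder on average?** Suppose every admitted pair were equally likely. This is an assumption, since the article gives no baseline distribution.

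- Part A totals sum to 2×2 + 4×3 + 3×4 + 2×5 + 1×6 = 44, so the mean is 44/12 = 3.67.
- Part B totals sum to 3×4 + 2×5 + 1×6 = 28, so the mean is 28/6 = 4.67.

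On that illustration part A is milder by one point, because its floor is lower. The real difference depends on who is enrolled.

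**The case against.** The strongest reply is that the text is comparative: part A is called milder relative to part B, and a floor at a total of 2 rather than 4 makes that plausible. The Discussion admits that the parts are not exclusive, and its limitations sentence speaks only of some patients with milder cough. The separation into parts rests mainly on the principle of one primary outcome per study, and Interventions justifies the two durations without mentioning severity. All of this stands. It means that the separation is not enforced; it does not show that the separation is absent.

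A reader might infer three stronger things that the documents do not support:

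- **That half of part A's patients are severe.** The 6 of 12 counts score patterns, and no patient distribution is given.
- **That part A's treatment comparison is biased.** Each part is randomised against its own placebo arm, so a mix of severities does not favour either arm.
- **That power is in danger.** Sample size reports a calculated need of 24 patients in part A, against 240 planned. The article gives no resolution rates by severity from which a loss could be worked out.

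It can also be said that strata for a log-rank test, and the routing of patients who qualify for both parts, may be set out in documents not shown. That is fair, and neither is claimed here as an omission. The finding is that the stated description and the stated criteria, both printed in the article, do not match.

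Finally, routing may matter at few sites. With 240 patients per part, 60 per centre in part A implies 240/60 = 4 centres, and 80 per centre in part B implies 240/80 = 3. That makes 7 centre slots for six centres, so if each centre runs at least one part, only one runs both. This is an inference. It does not close the gap, because a centre running only part A could still enrol severe cases.

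**Conclusion.** The point holds in a limited form. Table 4 does not enforce the milder population that Study participants describes for part A. Every score pattern eligible for part B is eligible for part A (6 of 12 patterns), including the maximum. This rests only on the score range and the two printed rules, and it survives either reading of and/or.

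The consequence is moderate. Part A may still be milder on average, and its comparison with placebo is valid with or without stratification. What remains is a primary outcome pooled over a baseline factor that the protocol itself treats as prognostic, and a milder/more severe contrast that cannot be relied on when the two parts are read together. The size of any dilution or extra censoring cannot be given from the documents.

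**What to change.** 1. Before unblinding, prespecify part A's primary log-rank test as stratified by baseline total cough symptom score (3 or less against 4 or more), unless the analysis plan already does so. Report the number of patients and the resolution results by arm in each stratum. The score is already collected at baseline, so no new data are needed. The cost is that one stratum may be small. Part A plans 60 placebo patients, and Randomization and blinding stratifies by centre, not by severity. An even split would give about 60 × 1/2 = 30 placebo patients per stratum; an uneven split would leave one stratum with fewer.

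2. Reconcile Study participants, Table 4 and the two Discussion passages (the rationale for separate parts and the limitations) so that the described populations match the criteria. This is a wording change. It does not replace the first step, because it leaves the analysis as it is.

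3. Whether to add an upper limit or a placement rule is for the sponsor. It would be a change of eligibility during recruitment: Trial status reports 318 of the 480 patients already included, so it could reach at most 480 − 318 = 162 across both parts.
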